#### 6.7.3.3 Expectedness

Expectedness will be determined by the Sponsor or designee. An AE will be considered unexpected if the event is not listed in the Reference Safety Information section of the current version of the IB.

### 6.7.4 Reporting of adverse event and serious adverse event

#### 6.7.4.1 Adverse event

AEs, which include clinical laboratory test results, will be monitored and documented from the time of informed consent until following the last administration of study drug through the Follow-up Period (Day 35). Subjects should be instructed to report any AE that they experience to the PI, whether or not they think the event is due to study drug. The PIs should make an assessment for each AE at each visit and record the event on the appropriate AE eCRF. Each AE should be followed until it resolves or until the end of the Follow-up Period.

Wherever possible, a specific disease or syndrome rather than individual-associated signs and symptoms should be identified by the PI and recorded on the eCRF. However, if an observed or reported sign or symptom is not considered a component of a specific disease or syndrome by the PI, it should be recorded as a separate AE on the eCRF. Additionally, the condition that led to a medical or surgical procedure (eg, surgery, endoscopy, tooth extraction, or transfusion) should be recorded as an AE, not the procedure itself.

Any medical condition already present at the Screening Visit should be recorded as medical history and not be reported as an AE unless the medical condition or signs or symptoms present at Baseline changes in severity, frequency, or seriousness at any time during the study. In this case, it should be reported as an AE.

Clinically significant abnormal laboratory or other examination (eg, echocardiogram) findings that are detected during the study or are present at the Screening Visit and significantly worsen during the study should be reported as AEs, as described below. The PI will exercise their medical and scientific judgement in deciding whether an abnormal laboratory finding or other abnormal assessment is clinically significant. Clinically significant abnormal laboratory values occurring during the clinical study will be followed until follow-up tests return to normal, stabilize, or are no longer clinically significant. Abnormal test results that are determined to be an error should not be reported as an AE. Laboratory abnormalities or other abnormal clinical findings (eg, echocardiogram abnormalities) should be reported as an AE if any of the following are applicable:

- If an intervention is required as a result of the abnormality;
- If an action taken with the study drug is required as a result of the abnormality; or
- Based on the clinical judgement of the PI.

#### 6.7.4.2 Serious adverse event

Collection of SAEs will only be up to 7 days following the last dose, however, follow-up on ongoing SAEs will continue until resolution or 4 weeks following the administration of the last dose of the study drug. After the 7 days reporting window, any SAE that the PI considers related to the study drug must be reported to Medpace Clinical Safety and the Sponsor/designee.

To report the SAE, complete the SAE form electronically in the eCRF. When the form is completed, Medpace Safety personnel will be notified electronically and will retrieve the form. If the event meets serious criteria and it is not possible to access the eCRF, send an email to Medpace Safety at **[contact]** or call the Medpace SAE hotline (phone number listed below) and fax/email the completed paper SAE form to Medpace (contact information listed below) within 24 hours of awareness. When the eCRF becomes available, the SAE information must be entered within 24 hours of the system becoming available.

The PI must continue to follow up the subject until the SAE has subsided or until the condition becomes chronic in nature or stabilizes (in the case of persistent impairment) or the subject dies.

Within 24 hours of receipt of follow-up information, the PI must update the SAE form electronically in the eCRF and submit any supporting documentation (eg, subject discharge summary or autopsy reports) to Medpace Clinical Safety via fax or email. If it is not possible to access the eCRF, refer to the procedures outlined above for initial reporting of SAEs.

Safety contact information Medpace Clinical Safety

Medpace SAE hotline – USA:

[contact], dial “3” or [contact], dial “3”

[contact] or [contact]

Email: [contact]

Medpace SAE hotline – Europe:

[contact]

[contact]

Email: [contact].

### 6.7.5 Pregnancy reporting

If a subject becomes pregnant during the study or within the Follow-up Period defined in the protocol, the PI is to stop dosing with study drug immediately and the subject should be withdrawn from the study. ET procedures should be implemented at that time.

A pregnancy is not considered to be an AE or SAE; however, it must be reported to Medpace Clinical Safety within 24 hours of knowledge of the event. Medpace Clinical Safety will then provide the PI/study site the Exposure In Utero (EIU) form for completion. The PI/study site must complete the EIU form and fax/email it back to Medpace Clinical Safety.

If the female partner of a male subject becomes pregnant while the subject is receiving study drug or within the Follow-up Period defined in the protocol, the PI should notify Medpace Clinical Safety as described above.

The pregnancy should be followed until the outcome of the pregnancy, whenever possible. Once the outcome of the pregnancy is known, the follow-up EIU form should be completed and faxed/emailed to Medpace Clinical Safety. If the outcome of the pregnancy meets the criteria for immediate classification as an SAE (ie, postpartum complication, spontaneous abortion, stillbirth, neonatal death, or congenital anomaly), the PI should follow the procedures for reporting an SAE.

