# 3 STUDY DESIGN

## 3.1 Overall Study Design

###### Cohort A

This is a minimum of one center, randomized, double-blind, placebo-controlled, pilot clinical study in the United Kingdom (Figure 1). The study will evaluate the efficacy and safety of AXA1125 in subjects with fatigue-predominant PASC (>12 weeks after initial infection).

The total study duration for each subject will be approximately 9 weeks. This study will comprise a Screening Period of up to 4 weeks, a Treatment Period of up to 4 weeks, and a Follow-up Period of 1 week.

After obtaining informed consent, subjects will be screened, and approximately 40 eligible subjects

(approximately 20 subjects per arm) will be randomized in a 1:1 ratio to receive BID oral administration of 33.9 g AXA1125 or a placebo. Doses will be self-administered on Days 1 to 28, inclusive. Subjects will have clinic visits on Day 1 and Day 28, as well as telephone visits on Day 14 and 1 week after completion of study product administration. Note: Doses should be self-administered at the clinic visit on Day 1 and Day 28 or End of Treatment (EOT)/Early Termination (ET).

The primary efficacy endpoint is the mean change from baseline at Week 4 in the PCr recovery rate following moderate exercise, as assessed by 31P-MRS, which will be evaluated at Screening and EOT/ET (Visit 4). Additional endpoints for assessment of muscle function, safety, tolerability, and exploratory efficacy endpoints will be assessed during the study

Details of randomization will be provided in the Randomization Plan and Interactive Response Technology (IRT) system.

Figure 1 Study Schematic - Cohort A

[figure not shown]

BID=twice daily; D=Day; MRS=magnetic resonance spectroscopy; PRO=patient-reported outcomes.

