## 3.4 Study Duration

**Cohort A**

Subjects will participate for up to 9 weeks. The study will comprise a Screening Period of up to 4 weeks, a Treatment Period of 4 weeks, and a Follow-up Period of 1 week. **Cohort B**

The total study duration for each subject in Cohort B will be approximately 6 weeks, which will comprise a Screening Period (1 week), Baseline Visit, a Treatment Period of 4 weeks, and a Followup Period of 1 week.

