   4. If a subject is of childbearing potential, must have a negative serum pregnancy test during Screening and agree to abstain from sexual activity or agree to use a highly effective form of birth control (failure rate <1% per year) for the duration of the study and for at least 30 days after the last dose of study drug
2. A male subject must meet the following criteria:
   1. Male subjects with a partner who is a female of childbearing potential (FCBP), must agree to abstain from sexual activity or agree to use a highly effective form of birth control (failure rate <1% per year) for the duration of the study and for at least 90 days after the last dose of study drug. Note: Female partner use of a highly effective form of birth control (failure rate <1%) is acceptable for male subjects participating in the study.
   2. Male subjects capable of fathering a child must agree to refrain from sperm donation for the duration of the study and for at least 90 days after the last dose of study drug.
3. A subject must agree to refrain from physical activity outside of normal activities of daily living before Day 1 and for the duration of the study
4. A baseline CFQ-11 total fatigue score (by Bimodal Scoring) of ≥8.

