## 5.3 Prevention of Pregnancy

Subjects who are FCBP or males with a partner who is a FCBP must use a highly effective form of birth control from the day of the first dose of study drug, throughout the study, and for 30 days (females) or 90 days (males) after the last dose of study drug.

Definition of Female of Childbearing Potential and of Fertile Men

A female is considered of childbearing potential (ie, fertile) following menarche and until becoming post-menopausal unless permanently sterile. Permanent sterilization methods include hysterectomy, bilateral salpingectomy, and bilateral oophorectomy.

A postmenopausal state is defined as no menses for 12 months without an alternative medical cause. A high FSH level in the postmenopausal range may be used to confirm a postmenopausal state in women not using hormonal contraception or hormonal replacement therapy. However, in the absence of 12 months of amenorrhea, a single FSH measurement is insufficient.

A man is considered fertile after puberty unless permanently sterile by bilateral orchidectomy Birth Control Methods Which May be Considered as Highly Effective

A highly effective method is one that can achieve a failure rate of <1% per year when used consistently and correctly. The acceptable birth control methods for female subjects are:

- Combined (estrogen and progesterone- [progestogen-] containing) hormonal contraception associated with inhibition of ovulation, administered by oral, intravaginal, or transdermal routes;
- Progesterone- (progestogen-) only hormonal contraception associated with inhibition of ovulation, administered by oral, injectable, or implantable routes;
- Intrauterine device;
- Intrauterine hormone-releasing system;
- Bilateral tube occlusion;
- Vasectomized partner (provided the partner is the sole sexual partner of the FCBP subject and that the vasectomized partner has received medical assessment of the surgical success); or
- Complete sexual abstinence (ie, refraining from heterosexual intercourse; the reliability of sexual abstinence should be evaluated in relation to the duration of this study and the preferred and usual lifestyle of the subject).

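### The protocol asks for notification of a partner's pregnancy for only 1 week after the last dose against a 90-day precaution period for men, and it leaves the reporting window for female subjects unclear

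*Protocol*

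**What the plan says.** Protocol 6.7.5 treats the two groups differently.

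- **Female subjects.** The opening sentence begins "If a subject becomes pregnant during the study or within the Follow-up Period defined in the protocol" and then tells the investigator to stop dosing and withdraw the subject. The next paragraph says that pregnancy is not itself an AE or SAE but must go to the safety group within 24 hours of the site learning of it. That paragraph names no end date.
- **Partners of male subjects.** The investigator should notify a pregnancy that begins "while the subject is receiving study drug or within the Follow-up Period defined in the protocol". Here the time limit is attached to notification itself.

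Sections 3.1 and 3.4 give the length of that period as "a Follow-up Period of 1 week". Section 6.7.4.1 places its end at Day 35.

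Section 5.3 requires highly effective contraception from the day of the first dose, "throughout the study, and for 30 days (females) or 90 days (males) after the last dose of study drug". The male inclusion criterion in 4.1 says the same: "for the duration of the study and for at least 90 days after the last dose of study drug". The ban on sperm donation also runs for 90 days.

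**The concern.** By setting 30 and 90 days, the protocol treats conception after the last dose as something to guard against for that long. Yet the only time limit written into the partner notification rule ends after 7 days, and the rule for female subjects can be read the same way.

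Contact with the subject stops early as well. The last scheduled pregnancy test is at Visit 4 (6.6.4.4) and the last scheduled contact is the Day 35 telephone call (Appendices 1 and 2).

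What is at stake is safety information. The Exposure In Utero form and the follow-up to pregnancy outcome both start from a reported pregnancy. Pregnancies in a trial of this size will be few, and each one is informative only if it is reported and followed.

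**Working it through.** **Inputs**

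- Dosing: "Doses will be self-administered on Days 1 to 28, inclusive" (3.1).
- End of Follow-up Period: Day 35 (6.7.4.1).
- Post-dose precaution period W: 30 days for women, 90 days for men (4.1, 5.3).
- Start of the precaution period: day of first dose (5.3).
- Window on Visit 4 and on Visit 5: plus or minus 3 days (Appendices 1 and 2).

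**Step 1: the plan's own figure.** Follow-up = Day 35 − Day 28 = 7 days, which agrees with the stated 1 week.

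**Step 2: days outside a 7-day rule.** Uncovered days = W − 7. As a share of the post-dose period this is (W − 7)/W. As a share of the whole precaution period from Day 1 it is (W − 7)/(28 + W).

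| | Women (only if the Follow-up wording governs reporting) | Men's partners (as written) |
|---|---|---|
| Uncovered days | 30 − 7 = 23 | 90 − 7 = 83 |
| Share of post-dose period | 23/30 = 77% | 83/90 = 92% |
| Whole period from Day 1 | 28 + 30 = 58 days | 28 + 90 = 118 days |
| Share of whole period | 23/58 = 40% | 83/118 = 70% |

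**Step 3: sensitivity to the visit window.** If the Visit 5 call falls 3 days late, the rule covers 10 post-dose days. The uncovered post-dose shares become 20/30 = 67% and 80/90 = 89%. If Visit 4 and the last dose are also 3 days early, it covers 13 days, and the shares become 17/30 = 57% and 77/90 = 86%.

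**Step 4: does another section close the gap?**

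- *Late SAE rule (6.7.4.2).* After 7 days, SAEs that the investigator considers related must still be reported. Section 6.7.5 sends spontaneous abortion, stillbirth, neonatal death, congenital anomaly and postpartum complication to SAE procedures, so these have a route if judged related. An uncomplicated pregnancy, or an outcome judged unrelated, does not.
- *Follow-up after withdrawal (4.5) and after stopping for an AE (4.5.3).* These run for at least 30 days and for 4 weeks respectively. Neither applies to a subject who completes treatment, and neither undertakes follow-up to 90 days.
- *End of study (8.5).* This is the last subject's visit across both cohorts. It gives no fixed post-dose window for an individual, and the partner sentence does not refer to the study as a whole.

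**The case against.** The best reply concerns women. In 6.7.5 the Follow-up Period wording governs stopping dosing and withdrawal. The duty to report stands in a separate paragraph and depends only on when the site learns of the pregnancy. On that reading a pregnancy on day 20 after the last dose is reportable. This stands: for female subjects the protocol is unclear, and it cannot be said to stop reporting at 1 week. The reply does not help partners, whose sentence limits notification directly.

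A reader might infer that most pregnancies in the precaution window would go uncaptured. The documents do not support that, for three reasons.

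- They give no pregnancy rate, so the shares are of days. Reading them as shares of pregnancies assumes an even risk per day.
- Section 5.3 starts the period at the first dose. For women the uncovered share is then 40% even on the unfavourable reading. Only for partners is it a majority (70%).
- The protocol does not prevent a site from reporting a later pregnancy. The exact statement is that notification is not expressly required.

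Nor do the documents show that the safety objective fails. Pregnancy is not among the safety endpoints in 2.3.3, and pregnancies during dosing and the following week are covered. Section 1.5.2.2 reports no accumulation in fasted amino acid levels on repeated dosing, so drug exposure in the later days is not established.

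Finally, the Safety Monitoring Plan (cited in 8.2.1.1) and the consent text are not available here and may contain further instructions. That limits any claim about what subjects are told. The wording of 6.7.5 still needs to agree with 4.1 and 5.3.

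**Conclusion.** The mismatch is real and clear for partners of male subjects: the notification rule leaves out 83 of 90 post-dose days (92%), or 83 of 118 days from first dose (70%). For female subjects it is conditional. If the Follow-up Period wording governs reporting, 23 of 30 post-dose days (77%), or 23 of 58 days from first dose (40%), are not expressly covered; if it does not, there is no gap.

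These figures assume the last dose on Day 28 and the follow-up call on Day 35. The partner result changes little with the visit windows. What is lost is the prompt for the Exposure In Utero form and outcome follow-up, for uncomplicated pregnancies and for outcomes judged unrelated. With about 50 subjects (40 plus 10) under required contraception, few events are to be expected, and no efficacy conclusion is affected. It is a wording inconsistency that bears on safety capture, and it is worth correcting because the correction is cheap.

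**What to change.** Reconcile 6.7.5 with 4.1 and 5.3. State one explicit reporting window for subject pregnancies and one for partner pregnancies, each matching the post-dose contraception period that the protocol already sets for that group. Keep this sentence separate from the instruction on stopping dosing and withdrawal, so that the reporting duty no longer depends on how the Follow-up Period wording is read. Ask the site to remind subjects at Visit 4 and on the Day 35 call to report a pregnancy in that period.

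The cost is about one sentence in 6.7.5 and a line in the visit instructions, with no added visit or test and no change to the contraception rules. The small downside is that safety reporting stays open after the last subject visit.

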### 6.7.6 Medical events of interest

No medical events of interest have been identified.

## 6.8 Efficacy Assessments

### 6.8.1 Phosphorus Magnetic Resonance Spectroscopy and Proton Magnetic Resonance

##### Spectroscopy (Cohort A Only)

31P-MRS and 1H-MRS will be performed prior to and following moderate exercise at Screening (Visit 1) and EOT/ET (Visit 4). The 31P-MRS and 1H-MRS acquisition protocol and guide is provided in the Study Reference Manual.

Note: A plasma analysis by 31P-MRS and 1H-MRS is not required to be performed at Screening if documentation of a plasma analysis by 31P-MRS and 1H-MRS was performed within 3 months of Screening and after 3 months of acute COVID-19 infection. If a historical 31P-MRS and 1H-MRS has been used to determine eligibility, then 31P-MRS and 1H-MRS should be repeated at Baseline to confirm eligibility and establish baseline.

31P-MRS is used to estimate the concentration of high-energy phosphate compounds; thus, the bioenergetic state of a tissue can be characterized in vivo. Accordingly, 31P-MRS can offer an alternative to histopathology for assessing the progression of the disease. The classic dynamic MRS experiment is to monitor the bioenergetic response of 31P metabolites to a sustained muscle contraction or exercise. To maintain the intracellular ATP concentration during this increased energy demand, PCr is depleted, inorganic phosphate (Pi) accumulates, and intracellular pH may also be modulated as a result of anaerobic glycolysis. Although the intracellular concentration of free (unbound) ADP is too low to be observed directly with 31P-MRS, it can be calculated indirectly, assuming equilibrium at creatine kinase. Upon cessation of exercise, each metabolite recovers to baseline levels. With relatively rapid (<8 seconds) time resolution and certain assumptions, a range of bioenergetic fluxes can be determined from the metabolic changes. In particular, a functional estimate of mitochondrial oxidative capacity can be calculated from the kinetics of PCr recovery rate. A recent study demonstrated the correlation between PCr, muscle strength, and walking speed in elderly subjects (Zane 2017).

MRS studies have demonstrated that muscle oxidative capacity is increased by endurance training, consistent with mitochondrial biogenesis and enhanced aerobic performance, and that the metabolic perturbations associated with exercise are attenuated. Bioenergetic deficits may predict clinical severity and are accompanied by decreased creatine content, as determined by 1H-MRS. Lipotoxicity influences mitochondrial function, and the amount of intramyocellular lipids increases in proportion to decreasing mitochondrial function. In a similar way, acetylcarnitine provides insights into fatty acid oxidation chains as a buffer for the pyruvate dehydrogenase flux. In addition, mitochondrial function is hampered at low intramuscular pH, and while the pH buffering capacity of skeletal muscle is very complex with several mechanisms involved, carnosine concentration (one of the metabolites responsible for pH buffering) has been shown to correlate with mitochondrial function. All of these metabolites can be non-invasively measured using 1H-MRS.

For additional information, refer to the Laboratory Manual.

### 6.8.2 Chalder Fatigue Questionnaire (CFQ-11 PRO for fatigue) (Cohort A and B)

This self-administered questionnaire will be provided to the subject at Screening (Visit 1), Visit 2, Visit 3, and EOT/ET (Visit 4). At Visit 3 (the telephone visit), it will be read to the subject or provided by secure electronic fashion. At all visits other than Screening, it will be performed before and after a 6MWT evaluation (Cohort A) and only before 6MWT evaluation (Cohort B).

### 6.8.3 6-Minute Walk Test (Cohort A and B)

The 6MWT assess the distance walked over 6 minutes as a submaximal test of aerobic capacity and endurance. The subject may take as many standing rests as they like, but the administrator should keep going and record the number of rests. If a subject requires assistance, only the minimum amount of assistance required for a subject to complete the task should be provided. The level of assistance if documented, however, should reflect the greatest amount of assistance provided. The administrator should walk behind the subject instead of beside or in front of the subject. This test should be performed at (or within 7 days of) Day 1 and EOT/ET (Visit 4). The subject may have clinic visit assessments performed over 2 days. The subject will be provided an overnight stay at a nearby hotel.

Detailed description of the 6MWT is provided in Study Reference Manual.

